*** Criteria for Peer-supporters:**

- Being HIV positive on ART, caretakers or social workers

- Being in good health condition

- Having good social skills

- Not having their children in study cohort.

- Living nearby or in the study regions.

*** Criteria for Social work supporter:**

- Having good social skills

- At least 2 years expertise of working with social support for HIV patients

*** Training curriculum for Peer-supporters and social work supporter:**

Session 1: Clinical Trial

Session 2: Basic HIV review
Session 3: Nutrition and HIV
Session 4: Opportunistic Infections
Session 5: Mental health
Session 6: Antiretroviral Therapy and Adherence
Session 7: Medication Adherence Support
Session 8: Role of the peer-supporters and social worker
Session 9: Setting boundaries and working as part of multidisciplinary team
Session 10: Disclosure
Session 11: Outreach overview
Session 12: Confidentiality
Session 13: Counseling skills
Session 14: Electronic study forms (CRF) and reports

Assignments for peer supporters

|  | **EST** | **CT** |
| --- | --- | --- |
| 1. Take part in the OPC management children/adolescent on ART(*) | Yes | Yes |
| 2. Group support meetings | Once per month per group | No |
| 2.2 Adherence assessment and reinforcement | Yes, over the phone | No |
| 2.3 Psychological support | Yes, over the phone | No |
| 2.4 Home visit once per month | Yes, and over the phone | No |
| 2.5 Arrange automatic reminder to give/take medicine | Twice a day depending on treatment regiment | No |
| 2.6 Telephone support to confirm time for home visit (at least 3 days in advance) and ask about the status of the patient. | One phone call weekly. Availability for the patient to call the supporter during working time and if emergency. |  |
| 2.7 Disclosure assessment and support | Yes | Yes, if needed |

*Note: (*) according to national guidelines*

**Indicators for Evaluation:**

The primary endpoint is time to virological treatment failure; the secondary endpoints are time to immunological and clinical treatment failure. In addition adherence will be assessed, risk factors of treatment failure will be evaluated and ART resistance mutations will be assessed. Adverse events including ARV adverse drug reactions, immune reconstruction inflammatory syndrome (IRIS) and OIs development, as well as Death/Mortality will be assessed. Loss of follow-up will be determined after the follow up period for patients who do not attend clinical visits and laboratory monitoring and will be analyzed as death. According to intention to treat patients that are absent one or more follow up visits and then turn up will be included in the analysis. Cost effectiveness will be assessed if there is a significant difference after two years follow up between the intervention and control group using costing analysis.

| No. | Indicator | Method of measurement | Method of assessment |
| --- | --- | --- | --- |
| 1 | Time to Virological treatment failure  (primary endpoint) | Viral load test:  -Baseline at enrollment  -Every 6 months of follow-up period | Cutoff (1): 1000 cps/ml (International)  - If the viral load Is above the cut off in the first assessment after 6 months of ART, it is defined as primary virological treatment failure, if the viral load is first suppressed and then detectable, it is referred as secondary virological treatment failure. |
| 2 | Time to Immunological treatment failure (secondary endpoint) | CD4 count:  - Recent result or baseline at enrollment.  Not part of routine follow up but if indicated due to virologic failure. | *Cutoff : below the level of severe immunodeficiency by age  -Child<11 months: % CD4<25%  -12 month <Child<35 months: %CD4<20%  - 35 months <Child<5 years: %CD4<15%  -Child>5 years: CD4 < 100 cell/mm3  *CD4 count falls to or below cutoff after initial recovery response (1). OR CD4 count falls rapidly below cutoff by age as confirmed by at least 2 consecutive times (2). OR CD4 count falls below more than 50% of the peak level during ARV treatment (3).  Decide %, the time length leading to immunological treatment failure in both group (EST & CT) |
| 3 | Clinical treatment failure (tertiary endpoint) | - Physical exam  - WHO scale in infant development (weight, height, physically active) | - Lack of or decline growth rate in children who initially respond to treatment (1).  - Loss of neurodevelopmental milestone or development of encephalopathy (2).  - Occurrence of new OIs or malignancies or recurrence of bacterial or fungal infections that refractory to treatment (3).  Decide %, the time length leading to clinical treatment failure in both group (EST & CT) |
| 4 | Adherence assessment | - Interview  - Questionnaire  - Pill count  - Pharmacy record | * Cut-off: (Good > 95%, Poor <95%)  - Good adherence: > 95% doses taken on time  - Poor adherence: < 95% doses taken OR > 95% doses taken but not on time.  * Other factors related:  - On time at every check-up visit  - Same caretaker at every check-up visit  - The current belief of caretaker to ART  - The current collaboration of child to ART  Decide % adherence in both group (EST & CT) |
| 5 | Risk factors of treatment failure | - Questionnaire  - Counseling | - Decide the pattern of risk factors of both groups and compare. |
| 6 | ART mutation assessment | - Genotyping (sequencing or real-time PCR for specific allele) | * ART mutation assessment for patients that have detectable viral load above 1000 copies/ml  * Baseline resistance will be assessed in a subsample of the cohort.  * Compare to Stanford HIV mutations database regarding to the regimens that patients were treated.  Decide pattern of mutation, % in both group (EST & CT) |
| 7 | ARV adverse effects | - Physical exam  - Lab test (enzyme) | Decide % of children having ARV adverse effects from both group (EST and CT) |
| 8 | IRIS | - Physical exam | Decide % of children having IRIS from both group (EST and CT) |
| 9 | OIs development | - Physical exam | Decide % of children having OIs development from both group (EST and CT) |
| 10 | Death/Mortality | - Regardless death causes | Decide % of children death from both group (EST and CT) |
| 11 | Development of AIDS events | - Physical exam | Decide % of children with development of AIDS events from both group (EST and CT) |
| 12 | Loss of follow-up  = Death (in analysis) | - Not able to manage within 6 months. | Assume as death/mortality in analysis.  These patients will be drawn out of study, If they come back to OPC, they will receive support as conventional procedure. |
| 13 | Physical development | Develop according to normal development |  |
| 14 | Quality of Life | - Assessment by caretakers and patients. | Using the PedQoL questionnaire adapted for different ages. |
| 15 | Cost effectiveness | - Collecting monetary data of expenses | - Cost: compare between EST to CT  - Effectiveness: % of patients with virological treatment failure |

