**Secondary Objectives:**

1. To compare the rate of and time to virological treatment failure (primary endpoint) immunological failure (secondary endpoint) /death/AIDS-associated events (tertiary endpoint) between the intervention and control group
2. To compare the rate of ART adherence between the intervention and control group
3. To compare the rate of acquiring OI’s, drug adverse effect, physical development, drug resistance between the intervention and control group.
4. To asses quality of life in intervention and control group before and after intervention
5. To assess cost effectiveness of peer support comparing to conventional care

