**Sample size:**

WHO sample formula for the intervention study, comparing to 2 proportions

We assume the possibility of treatment failure of 15% in the control arm and 10% in the intervention arm after 2 years of follow-up. With 80% power and a test at the two-sided 5% significance level, 10% losses of follow-up, approximately 540 patients are required **(260 per group)** into the trial.

**Enrollment:** All patients aged 10-18 years meeting the inclusion criteria are eligible at the study sites will be enrolled.

**Randomization:** The patients are randomized in the intervention or control group the first time of the intervention. E.g. all patients that attend the examination at a specific weekday will be included in intervention group other week day will be the control group. The peer group meetings will then be organized according to the day of examination where each group contain about 15 patients. Patients can/will not know which day is which until they come to avoid bias. Written consent will be done.

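### Cost-effectiveness is promised without condition as an objective, but is to be analysed only after an undefined significant difference, so it goes unanswered or rests on an effect that is too large on average

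*Protocol*

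**What the plan says.** Three places in the protocol bear on the economic question.

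- **Secondary Objectives, item 5**, with no condition: "To assess cost effectiveness of peer support comparing to conventional care".
- **Indicators for Evaluation, table, indicator 15**, also with no condition. The measurement is "Collecting monetary data of expenses", costs are compared between the two arms, and the effect measure is "Effectiveness: % of patients with virological treatment failure".
- **Indicators for Evaluation, opening paragraph**, with a condition: "Cost effectiveness will be assessed if there is a significant difference after two years follow up between the intervention and control group using costing analysis".

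The conditional sentence does not say which endpoint must differ or at what level. The same paragraph says that "The primary endpoint is time to virological treatment failure", while the later Evaluation section gives a composite of virological failure, death and AIDS-associated events. The protocol does not say what becomes of objective 5 if the difference is not significant.

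**The concern.** An economic evaluation estimates the extra cost, the extra effect and the uncertainty of both. A non-significant difference does not show that the arms are equally effective. The costs differ in any case, because the intervention arm receives group meetings, home visits and weekly calls that the control arm does not. The Protocol Précis justifies the trial by the need for cheap, sustainable support, so readers will want the cost and the plausible range of benefit whichever way the test falls.

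Making the analysis depend on significance has two effects. In trials that miss significance, a declared objective gets no answer. In trials that reach it, the effect estimate has passed a filter that favours large values, so on average cost per failure avoided looks lower than it is. Because the trigger is undefined, the choice of which difference opens the analysis could also be made after the results are known.

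**Working it through.** **Inputs (protocol, Sample size).** The plan assumes "treatment failure of 15% in the control arm and 10% in the intervention arm after 2 years of follow-up". It continues: "With 80% power and a test at the two-sided 5% significance level, 10% losses of follow-up", and "approximately 540 patients are required", with 260 per group in brackets. Allocation is 1:1, so 540 means 270 per arm; 2 × 260 = 520. Both 260 and 270 are used below. The trigger is taken to be a two-sided 5% test of failure at two years, which is an assumption because the conditional sentence does not define it.

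**1. The stated size.** For two proportions with pooled variance:

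n = [1.96·√(2·0.125·0.875) + 0.8416·√(0.15·0.85 + 0.10·0.90)]² / 0.05² = 685.6, so 686 per arm.

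With 10% loss, 686/0.9 = 762.2, so 763 per arm or 1,526 in total. The stated 540 is not reproduced. That is a separate point, used here only to size the consequence.

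**2. How often the analysis would be run.** Power = Φ{[0.05·√n − 1.96·√0.21875] / √0.2175}.

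- n = 270: (0.8216 − 0.9167)/0.4664 = −0.204, giving 41.9%.
- n = 260: (0.8062 − 0.9167)/0.4664 = −0.237, giving 40.6%.
- n = 686: (1.3096 − 0.9167)/0.4664 = 0.842, giving 80.0%.

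A log-rank approximation (hazard ratio ln 0.90/ln 0.85 = 0.648, events = 2n × 0.125) gives 43% and 42% at 270 and 260.

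**3. Why the effect is inflated.** At 270 per arm the smallest difference that is significant is about 1.96·√(0.21875/270) = 5.6 points (5.7 at 260). This exceeds the assumed true difference of 5.0, so significance is reached almost only by overestimates.

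**4. Size of the inflation.** 2,000,000 simulated trials per size, true rates 15% and 10%, two-sided pooled z-test at 5%. The understatement is one minus the average of 0.05/(observed difference) over significant trials, which assumes a fixed incremental cost.

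| Per arm | Significant benefit | Mean difference if significant | Ratio to 5.0 | Understatement of cost per failure avoided |
|---|---|---|---|---|
| 260 | 40.9% | 7.7 points | 1.55 | 33% |
| 270 | 41.7% | 7.6 points | 1.53 | 32% |
| 686 | 80.2% | 5.6 points | 1.12 | 6% |

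Over all trials, significant or not, the mean difference is 5.0 points at every size. The distortion comes from the condition alone, and its size depends on the power.

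**5. Losses counted as failures.** Statistical Considerations counts death and loss to follow-up as failure. Assuming 10% loss in both arms, the rates become 0.15 × 0.9 + 0.10 = 23.5% and 0.10 × 0.9 + 0.10 = 19.0%. At 270 per arm:

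Φ{[0.045·√270 − 1.96·√(2·0.2125·0.7875)] / √(0.235·0.765 + 0.19·0.81)} = Φ{(0.7394 − 1.1339)/0.5776} = Φ(−0.683) = 25%.

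The analysis would then be run in about one trial in four.

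**The case against.** **An objective may be staged.** Item 5 is one line in a list of aims, and the later sentence can be read as saying when that aim will be pursued. Staging is a legitimate design choice, but the protocol does not present it as one: indicator 15 repeats the commitment without condition, and nothing says how objective 5 is reported if the condition fails. The two texts remain unreconciled.

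**Most of the size belongs to the sample-size error.** This stands. At a true 80% power about 20% of trials would drop the analysis, with about 12% inflation and 6% understatement. The inconsistency and the objection of principle remain, but the large figures depend on the planned 540.

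**Stronger readings that the documents do not support.**

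- A reader might infer that the trigger is p < 0.05 on the primary endpoint. The two-year horizon and indicator 15 make that plausible, but neither is written, and the primary endpoint itself is stated in two ways.
- A reader might infer that any cost-effectiveness result from this trial must be exaggerated. Under the assumed rates nearly all significant trials overestimate (more than 99.8% at 260 to 270 per arm). The true difference is unknown, however, and a larger one would be inflated less.
- A reader might infer that the protocol is deficient for not naming a bootstrap or an acceptability curve. Those are method choices for a later plan. They would also need patient-level costs, and neither the flow chart nor the questionnaires shown list a cost item.

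**Conclusion.** The point holds. The conditional sentence conflicts with objective 5 and indicator 15, and its trigger is undefined. At the protocol's rates and 260 to 270 per arm, objective 5 would go unanswered in about 58 to 59% of trials even if the hoped-for benefit is real. In the rest the effect would be about 53 to 55% too large on average, and cost per failure avoided about 32 to 33% too low.

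These figures rest on three assumptions: a two-sided 5% test on failure at two years, a fixed incremental cost (the protocol gives no cost figures), and the planned size. A corrected sample size would remove most of the distortion but would still leave about one trial in five without an economic answer. Counting an assumed 10% loss in each arm as failure leaves about three in four without one. The primary analysis is not affected.

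**What to change.** In the opening paragraph of Indicators for Evaluation, delete the significance condition. State instead that incremental cost and incremental effect (the percentage with virological failure, as in indicator 15) will be estimated by randomised group, with their uncertainty, whatever the result of any significance test. This brings the paragraph into line with objective 5 and indicator 15 and removes the need to define a trigger.

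The cost is some extra analysis work on the expense data that indicator 15 already plans to collect for both arms. It needs no extra patients or visits. The protocol does not say whether expenses are recorded per patient or per arm, so the method for expressing uncertainty should follow the level at which they are recorded and can be left to a later plan.

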**Study Designs:**

Randomized controlled trial, multi-center study

Randomization will be 1:1 and stratified by center and ART status at enrolment stratified according to naïve vs. on ART treatment.

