**Study Regions:**

- Hanoi and Ho Chi Minh city

**Study Size:**  Planned enrollment of a total of 540 HIV positive children 10-16 years of age, on ART and randomize to either Enhanced Treatment Support (ETS) or Conventional Treatment (CT).

**Study Duration:** Study enrollment at the second quarter of 2019 and the study will be completed when all patients have completed follow up during 24 months.

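### The virological-failure definition leaves two things open: whether loads below 1000 copies/mL count as secondary failure, and how children already above 1000 at enrolment are counted; the ART-status stratum also contradicts the stated population

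*Protocol*

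**What the plan says.** All references are to the Protocol.

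- **Threshold.** Indicators for Evaluation, indicator 1 (time to virological treatment failure, marked as the primary endpoint) opens with "Cutoff (1): 1000 cps/ml (International". A load "above the cut off in the first assessment after 6 months of ART, it is defined as primary virological treatment failure". For the other limb, "if the viral load is first suppressed and then detectable, it is referred as secondary virological treatment failure". No value is attached to 'suppressed' or to 'detectable'.
- **Use of the same word elsewhere.** Indicator 6 (ART mutation assessment) reserves genotyping for detectable loads and adds that these are above 1000 copies/mL.
- **Eligibility.** The inclusion and exclusion criteria cover clinic follow-up, age, temporary referral and institutional care. They mention neither viral load nor ART.
- **Measurement.** Viral load is taken at baseline and every 6 months to month 24 (indicator 1; Interval laboratory test; Appendix 1B).
- **Analysis.** Statistical Considerations plans intention to treat, survival analysis, regression on group plus unnamed patient characteristics, and a stratified analysis whose strata are not named.
- **ART status.** Study Designs says "Randomization will be 1:1 and stratified by center and ART status at enrolment stratified according to naïve vs. on ART treatment". Study Size describes 540 children "on ART and randomize to either Enhanced Treatment Support (ETS) or Conventional Treatment (CT". Appendix 1B makes the adherence assessment conditional on the child already being on ART.

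**The concern.** In a cohort described as on ART, secondary failure is the limb that applies to children who are treated and suppressed, and that limb lacks an explicit threshold. A child with a low but detectable load at month 12 is a primary-endpoint event on one reading and event-free on the other.

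The primary-failure limb does not fill the gap for children who enter viraemic. For a child treated for years, the first assessment after 6 months of ART normally lies before the trial. If that child is above 1000 at enrolment, the text permits an event at or near time zero. If the child has never been suppressed, it permits no classification at all. Under intention to treat the child is still analysed.

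Two things are at stake. Events already present at entry cannot be prevented by the intervention, and low-level loads may not respond to it; both dilute the contrast. A chance imbalance in baseline viraemia between the arms would also bias the primary comparison unless the analysis accounts for it, and baseline viral load is not named as a stratum or covariate.

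**Working it through.** **Step 1: the plan's own figure.** Inputs from Sample size: "We assume the possibility of treatment failure of 15% in the control arm and 10% in the intervention arm after 2 years of follow-up"; two-sided 5%, 80% power, 10% loss, total about 540. The usual two-proportion formula gives 686 per arm, or 1372 evaluable. Dividing 686 by 0.9 gives 763 per arm, or 1526 enrolled. The stated 540 is not reproduced. That is a separate error; here it matters only because it sets the starting power.

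**Step 2: starting power at 270 per arm (540/2).** Power = Φ[(d − 1.96·SE0)/SE1], with SE0 = √(2p̄(1−p̄)/n) and SE1 = √([p1(1−p1)+p2(1−p2)]/n).

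With p1 = 0.15, p2 = 0.10 and n = 270: SE0 = 0.02846, SE1 = 0.02838, (0.05 − 0.05579)/0.02838 = −0.204, so power = 42%.

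**Step 3: enrolment viraemia counted as failure.** The protocol gives no share v viraemic at entry; v = 5-10% is an assumption. Suppose these children are events in both arms and the rest keep 15% versus 10%. Then p = v + (1−v)·p0. The pooled share of events already present is 2v/(p1+p2).

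| v | Control | Intervention | Share of all events | Power |
|---|---|---|---|---|
| 5% | 0.05+0.95×0.15 = 19.25% | 0.05+0.95×0.10 = 14.5% | 10/33.75 = 30% | 31% |
| 10% | 23.5% | 19.0% | 20/42.5 = 47% | 25% |

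Sensitivity: suppose instead that the 15% already includes v and only new failures fall by one third. Then v = 5% gives 15% versus 11.7% and power 21%; v = 10% gives 15% versus 13.3% and power 8%.

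**Step 4: low-level loads counted as secondary failure.** Assume a rate b per visit of 1-3%, independent over four visits and unaffected by the intervention. Then B = 1 − (1−b)⁴ and p = p0 + B(1−p0).

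| b | B | Control | Intervention | Power |
|---|---|---|---|---|
| 1% | 3.9% | 18.3% | 13.5% | 33% |
| 2% | 7.8% | 21.6% | 17.0% | 27% |
| 3% | 11.5% | 24.8% | 20.3% | 23% |

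**Step 5: ART status, side by side.** Under Study Size the naive stratum is empty by definition. Under the inclusion criteria and Appendix 1B it may contain children, in unknown number. Study Designs presupposes that it does. These passages cannot all describe the same population.

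**The case against.** Several stronger statements are tempting, and the document does not support them.

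- **That any detectable load is the settled rule for secondary failure.** The 1000 cut-off heads the cell that contains both limbs, it is the only virological threshold given, and indicator 6 pairs 'detectable' with above 1000. The authors may well mean 1000 throughout. Equally, the qualifier in indicator 6 would be redundant if 'detectable' already meant above 1000. What stands is an ambiguity in the primary event.
- **That children viraemic at entry are put into the event count.** No passage says so. A child never suppressed does not meet the secondary limb, and the primary limb may lie in the past. Their status is undefined.
- **That baseline viral load goes unadjusted.** Statistical Considerations plans regression with patient characteristics, and the covariate list may belong in an analysis plan that is not at hand. One can say only that the protocol does not name it.
- **That the naive stratum is nearly empty.** It is empty under one passage and of unknown size under others. Only the contradiction is documented.

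The power figures are also open to challenge. Their inputs are assumed. Persistent low-level viraemia in the same children would add fewer events than independence implies, and an intervention aimed at adherence might reduce low-level loads. The 42% base reflects the sample-size error, so only the fall from 42% belongs to this point. These objections limit the size of the effect; they do not remove the ambiguity or the gap.

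**Conclusion.** The point holds as one of ambiguous and incomplete definition, not as a rule shown to miscount events. The secondary-failure limb does not repeat the 1000 cut-off and leaves 'suppressed' undefined. The primary-failure limb runs on an ART clock, so children above 1000 at randomisation have no defined status. Because this is the protocol's working definition of the primary endpoint, both gaps should be closed in the protocol itself. The ART-status contradiction is real but secondary.

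The size is illustrative. From a base of 42% at 270 per arm, power would fall to about 31-25% if 5-10% enrolment viraemia were counted, or to about 33-23% if low-level loads arose in 1-3% of children per visit. Both ranges rest on event rates that the protocol does not supply and, for the second, on independence across visits and no effect of the intervention on such loads.

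**What to change.** 1. Use one threshold, viral load above 1000 copies/mL, for primary and secondary failure, and define 'suppressed' by the same value. 'Above' keeps the protocol's own boundary.
2. Set time zero at randomisation and count only post-randomisation loads, from month 6.
3. Stratify or adjust the primary Cox/log-rank analysis by baseline viral load (≤1000 versus >1000).
4. Pre-specify a supportive analysis in children suppressed at baseline. It is needed because a child viraemic at entry and still viraemic at month 6 remains in the primary count; step 3 limits imbalance but does not remove such events.
5. Reconcile Study Designs, Study Size, the inclusion criteria and Appendix 1B on ART status, and drop the naive/on-ART stratum if all participants are on ART.

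Baseline viral load is better handled in the analysis than as a new randomisation stratum, because the allocation by clinic weekday described under Sample size could not deliver such a stratum.

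The cost is protocol wording and slightly more analysis work. Baseline viral load is already scheduled for every child. Fewer events will be counted than under the literal reading.

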**Peer Support Intervention**

**Follow-up 24 months**

**Analysis**

**Appendix 1 B: Trial Flow Chart for both groups (EST and CT)**

|  |  |  | **24 months follow-up**  **Every 6 months = 6 interval assessment** | | | |
| --- | --- | --- | --- | --- | --- | --- |
| **Event** | **SCR** | **Baseline or enrollment** | **1^st^** | **2^nd^** | **3^rd^** | **4^th^** |
| Informed Consent | x |  |  |  |  |  |
| Inclusion/Exclusion Criteria | x |  |  |  |  |  |
| Medical History | x |  |  |  |  |  |
| Clinical Assessments (vital signs, weight, physical exam) |  | x | x | x | x | x |
| Medication Adherence Assessment (if under ART already) |  | x | x | x | x | x |
| Adverse Event Assessment |  | x | x | x | x | x |
| CBC |  | x | x | x | x | x |
| Liver Enzymes Tests |  | x | x | x | x | x |
| AFB sputum (if available) |  | x | If (indicated) | | | |
| CD4 (if available) |  | x |  |  |  |  |
| Viral load |  | x | x | x | x | x |
| Genotype resistance  (0.5 ml plasma) |  | x | If (indicated) | | | |
| -80 oC Stored plasma  (0.5 ml plasma) |  | x | X | X | x | x |

Volume of Blood sample: 3-4 ml/time, assuming having 1.5 ml of plasma enough for VL, genotypic and storage

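### Time to immunological failure is to be compared between arms, but CD4 after baseline is prompted only by virological failure, so its detection depends on an outcome the intervention is meant to change

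*Protocol*

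**What the plan says.** Secondary Objectives, item 1, plans to compare the rate of and time to several outcomes, among them "immunological failure (secondary endpoint) /death/AIDS-associated events (tertiary endpoint) between the intervention and control group". Indicators for Evaluation repeats this: "the secondary endpoints are time to immunological and clinical treatment failure". Row 2 of its table asks for the percentage failing and the time to failure in both groups.

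The same row gives the CD4 source as "Recent result or baseline at enrollment" and says of later CD4: "Not part of routine follow up but if indicated due to virologic failure". The flow chart in Appendix 1B marks CD4 once, at baseline and subject to availability. The four follow-up columns are blank for CD4, whereas viral load is marked at every visit and the sputum and genotype rows allow follow-up tests when indicated.

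Row 2 offers three alternative failure criteria: a fall to or below the cutoff after an initial recovery; a rapid fall below the cutoff confirmed at least twice in succession; or "CD4 count falls below more than 50% of the peak level during ARV treatment".

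**The concern.** A time-to-event comparison needs the event to be looked for in the same way in both arms. Here the trigger for looking is virological failure, which is the primary endpoint in Indicators for Evaluation and a component of it in the Synopsis and Evaluation sections. The intervention is meant to reduce it. If it does, fewer ETS children have CD4 measured, and fewer immunological failures are detected in that arm even if CD4 behaves identically among children who are not tested.

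The timing is affected too. An event found by a triggered test carries a date no earlier than virological failure, so the time to it largely reflects when viral load crossed its threshold. A lower hazard under ETS could not be separated into a difference in immunological failure and a difference in testing.

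**Working it through.** **No figure to reproduce.** The protocol gives no rate, event count or power for immunological failure. The check sets the criteria against the schedule and then sizes the effect from the protocol's own failure rates.

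**Criteria against schedule.** All three criteria need at least one CD4 value during follow-up. Only the second needs two consecutive values, and no second test is scheduled. A child who first fails virologically at the fourth and last visit has no later study visit in Appendix 1B for confirmation. The first and third could be met by one triggered value set against an earlier recovery or peak, if the medical record holds one.

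**Inputs**
- Treatment failure at 2 years: 15% CT, 10% ETS (Sample size). Read here as virological failure, which is an assumption because the section says only treatment failure.
- Allocation 1:1 (Study Designs).
- Size: 540 in total, or 260 per group (Sample size). These differ, since 2 × 260 = 520, but the share below does not depend on which is used.
- Immunological failure among virological failures: 13.7% (Protocol Précis, from a pooled analysis). Illustration only.

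**Children with a protocol-triggered CD4 after baseline**
- At 270 per arm: CT 270 × 0.15 = 40.5; ETS 270 × 0.10 = 27; together 67.5 of 540 = 12.5%.
- Without one: 540 − 67.5 = 472.5, or 87.5%.
- At 260 per arm: 39 + 26 = 65 of 520; without one 455, again 87.5%.
- If the 15% and 10% also include deaths or AIDS events, virological failure is rarer and the untested share exceeds 87.5%.

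**Detected ratio.** Let q be the risk of immunological failure given virological failure, equal in both arms, with deaths and losses not counted as events.

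Detected ETS/CT ratio = 0.10q / 0.15q = 0.67, for any q.

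With q = 13.7% and 270 per arm, the detected events are 270 × 0.15 × 0.137 = 5.5 in CT and 270 × 0.10 × 0.137 = 3.7 in ETS, about 9 in the whole trial.

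**How far that may lie from the truth.** Let r be the risk of immunological failure without virological failure, assumed equal in both arms.

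True ratio = (0.10q + 0.90r) / (0.15q + 0.85r)

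| q | r = 0.5% | r = 3% | Detected |
| --- | --- | --- | --- |
| 5% | 0.81 | 0.97 | 0.67 |
| 13.7% | 0.73 | 0.88 | 0.67 |
| 30% | 0.70 | 0.81 | 0.67 |

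For q = 13.7%, the share of events missed is 0.85r / (0.15q + 0.85r) = 17% to 55% in CT and 0.90r / (0.10q + 0.90r) = 25% to 66% in ETS, as r goes from 0.5% to 3%. The protocol gives no value for r, so the range is an assumption. At r = 0 the true ratio is also 0.67 and nothing is missed.

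**The case against.** Several points on the other side stand, and they limit the claim.

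- **Other CD4 values may exist.** Interval laboratory test leaves other tests to national guidelines, row 2 accepts a recent result, and Data Management makes medical records and laboratory reports source documents. A reader might infer that a child without virological failure can never be counted, or that the on-treatment peak is never known. The documents do not support that. They do support that no such values are scheduled and that row 2 calls CD4 non-routine, so any extra values would be sporadic rather than common to both arms.
- **Something can be counted.** Immunological failure detected after virological failure can be tallied in all randomised children. It is a narrower quantity than the endpoint named in Secondary Objectives, and its detection still depends on the primary outcome.
- **A ratio of 0.67 need not be an artefact.** If CD4 falls mainly through virological failure, fewer virological failures mean genuinely fewer immunological failures. The figure also needs equal q in the two arms. The existence of the bias rests on the schedule; its size rests on assumptions.
- **Deaths and losses may count.** Statistical Considerations treats death and loss to follow-up as failure without limiting this to the primary endpoint. With 10% loss in each arm and q = 13.7%, the ratio becomes (0.0137 + 0.10) / (0.0206 + 0.10) = 0.94. So it is not established that the comparison would simply repeat the virological one. Events would then mostly be losses (10% of 540 = 54, against about 9), which tells little about CD4.

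A reader might also infer that the result is to be offered as independent support for the primary finding. The protocol does not say so.

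**Conclusion.** The point holds in this form: the protocol plans a between-arm comparison of time to immunological failure, while its CD4 schedule makes detection depend on virological failure. The analysis plan cannot repair this, because most of the values would not be collected.

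The 87.5% without a protocol-triggered CD4 rests on reading the planned failure rates as virological. The 0.67 rests further on equal q in both arms and on leaving deaths and losses out. Neither is a forecast. It would go too far to say that immunological failure cannot be estimated at all; what cannot be had is an unbiased comparison of the endpoint as named, in all randomised children. The primary endpoint is unaffected, so this should be corrected but does not threaten the trial's main conclusion.

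**What to change.** **Preferred.** Remove time to immunological failure from the between-arm secondary endpoints in Secondary Objectives item 1 and in Indicators for Evaluation (opening paragraph and row 2). Report CD4 and immunological failure descriptively among children with virological failure, by arm, stating that this group is selected after randomisation. This changes wording only; the cost is one fewer comparative secondary endpoint.

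**Alternative.** Keep the comparison only if CD4 is measured at fixed common visits in both arms, for example with the 6-monthly viral load, using only the failure criteria those values can support. This adds assay cost. It also requires checking that CD4 is available at the sites and that the blood volume suffices: Appendix 1B budgets 3–4 ml per draw for viral load, genotyping and storage and does not mention CD4.

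Either way, Secondary Objectives, row 2 and the CD4 row of Appendix 1B should be brought into agreement; at present the flow chart does not show even the triggered test that row 2 allows.
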